### Neurofilament light as a pharmacodynamic marker

We designed an experimental medicine study, relying on the circulating marker of axonal damage neurofilament light (NfL) to assess MSC efficacy. In the context of TBI, measurement of circulating NfL has shown prognostic utility after mild [41, 42] and severe TBI [43]. Compared to GFAP, UCH-L1, and S100B that show prognostic values (GFAP [42, 44], UCH-L1 [44, 45], S100B [45]) and may inform on computed tomography (CT) abnormalities (as for GFAP [46–48]), NfL has the advantage of different temporal trajectory with a progressive increase in plasma levels over the first 2 weeks after injury [49, 50]. Importantly, initial serum NfL levels are predictive of clinical outcome (Glasgow Outcome Scale extended score, GOSE) at 12 months after injury in severe TBI [49] and correlate with brain volumes and magnetic resonance imaging (MRI) measures of white matter (WM) axonal integrity [50, 51]. NfL has shown validity as a pharmacodynamic biomarker in monitoring treatment response after acute or chronic neurological disorders [52–54]. Thus, NfL is now emerging as a blood biomarker with diagnostic and prognostic utility for TBI patients and may inform the efficacy of experimental medicine studies.

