### Secondary objectives

Secondary objectives will assess the biological activity of intravenous infusions of allogeneic MSCs in terms of modification of the following clinical variables and biological parameters:Brain injury evolution and white matter damage by advanced longitudinal MRI (with morphological sequences including T1, T2 as well as FLAIR, SWI, DWI, and DTI for quantification of traumatic axonal injury) acutely (4 days) subacutely (14 days) and at 6 month post-TBI to provide a detailed description in atrophy, diffusion and myelin integrity.Brain immunomodulatory changes by temporal profiling (daily for 3 days after TBI, at days 7 and 14 and at 1, 6 and 12 months) of circulating biomarkers of structural damage (including NfL and GFAP), neuroinflammation (i.e., IL-6, IL-10, TNFα) and vascular integrity (i.e., MMP9).Clinical outcome by a structured clinical and neuropsychological outcome assessment at both 6 and 12 months, by Glasgow Outcome Scale Extended (GOSE) and Quality of life after brain injury (QOLIBRI) test.

The timepoints for the secondary outcome measurements are shown in Fig. 2.

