## Methods

### Study setting

About 78 adult TBI patients admitted in intensive care units (ICU) will be enrolled in 3 centers: the Fondazione IRCCS San Gerardo dei Tintori Monza, the Fondazione IRCCS Cà Granda Ospedale Maggiore Policlinico Milano and the ASST Ospedale Papa Giovanni XXIII Bergamo. Patients will be enrolled if fulfilling the eligibility criteria listed in Table 2.

**Table 2 Tab2:** Eligibility criteria

Inclusion criteria	Exclusion criteria
– Age: 18–70 years (inclusive) – Clinical frailty index < 5 [60] – Evidence of TBI confirmed by abnormalities consistent with trauma on CT scan upon admission (Marshall’s CT Classification > 1) – Study drug (MSCs/placebo) administration start within 48 h from TBI – GCS ≤ 8 at recruitment and at least one pupil reactive to light – ICP monitoring, already inserted or planned for clinical indications – Weight < 100 kg and > 40 kg	– Motor GCS > 5 at recruitment – High likelihood (> 85%) of death in the first 48 h calculated by IMPACT calculator [61] on early admission data – Bilateral unreactive mydriasis – Opening ICP > 40 mmHg – Known history of prior brain injury, psychiatric disorder, neurological impairment and/or deficit – Brain penetrating injury – Spinal cord injury – Epilepsy requiring ongoing anti-convulsant therapy – Severe organ failure (including PaO_2_/FiO_2_ < 200 and shock) – Recent serious infectious process requiring ICU admission – Cancer (ongoing) – Immunosuppression – Human immunodeficiency virus – Positive urine pregnancy test or breastfeeding – Known risk/history of coagulopathy and thromboembolism – Pre-existing and severe: ▪ Lung disease (such as asthma, chronic obstructive pulmonary disease) ▪ Heart dysfunction (as heart failure and reduced cardiac output) ▪ Liver insufficiency (as cirrhosis) ▪ Kidney insufficiency ▪ and other organ severe abnormalities – Known hypersensitivity to excipients used in the formulation (dimethyl sulfoxide, DMSO; citrate-dextrose solution, ACD) – Participation in a concurrent interventional study

CT, computed tomography; GCS, Glasgow Coma Scale; ICP, intracranial pressure; ICU, intensive care unit; IMPACT, international mission for prognosis and clinical trial; MSCs, mesenchymal stromal cells; TBI, traumatic brain injury

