### Statistical design and sample size

The statistical study design is conceived in 2 steps.

#### Step 1

An interim safety analysis will be performed to evaluate separately in each of the two experimental dosage groups, at a one-sided type I error rate of 10%, whether more than 30% of patients experience at least one SADR within 14 days from treatment and at the same time at a power of 80% whether 5% or less of the patients do not experience any SADR. Adopting the Fleming design with A’Hern’s approach, 12 evaluable patients will be analysed in each group. The maximum number of patients experiencing at least one SADR to observe in each experimental group is 1 out of 12, since this result is associated with an upper limit of the 80% exact confidence interval of 28.8%. The experimental treatment would be considered safe for this step only if none or one patient experimented with a SADR.

According to the above roles:If both experimental treatments are unsafe, the study will be stopped for safety issues, and step 2 will not be performed.If one experimental treatment is considered safe and the other not, only the safe arm will proceed with step 2 of the study.If both the experimental dosages are safe, the more active schedule will be selected for step 2.

The more active schedule will be defined in terms of the proportion of patients who reaches an NfL increase at 14 days equal to or lower than the baseline level by five folds (defined as “responder patient”). This cutoff has been determined based on longitudinal quantification provided by BIO-AX-TBI collaborators [50], showing a median increase of 12.8-fold at 14 days compared to baseline, with the first quartile equal to a fivefold increase. The experimental arm with a higher frequency of responders will be selected as the most promising in terms of activity and it will be chosen for the second step. In the case of an equal number of responder patients in the two experimental arms, the cutoff defining the response will be increased by 1 unit iteratively, since a difference between the two experimental arms will be observed. This assessment will only be performed on the MSC-treated arms; the control group will not be considered. According to Simon, Wittes and Ellemberg randomised phase II design [56], the study has more than an 80% probability of correctly selecting the more active schedule when the proportion of responder patients is 15% higher in the first of the two treatment schedules.

#### Step 2

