The endpoint will be the NfL at 14 days. The final analysis of biological activity will be performed by increasing the sample size to 27 evaluable patients in the experimental and control arms. The study is designed to detect an effect size of 0.59 on the logarithmic scale of the experimental to control arm, setting a one-sided type I error rate of 10% and a power of 80%.

Therefore, the total number of evaluable patients to be analysed will be 66 (27 in the control arm, 12 in the experimental arm stopping at the first step and 27 in the experimental arm reaching the second step). Expecting 13% of deaths of TBI patients in ICU [2], the number of patients to be randomised is about 78 (32 in the control arm, 14 in the experimental arm stopping at the first step and 32 in the experimental arm reaching the second step). After the trial closure after the first step, the number of patients to randomise will be about 42 (14 in each arm).

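### Step 1 picks the dose on a dichotomised fold-rise from baseline, although Step 2 tests the day-14 NfL level; a baseline-adjusted day-14 comparison would select more reliably at little cost

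*Protocol article*

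**What the plan says.** Under Statistical design and sample size, Step 1, if both doses pass the safety rule the more active one goes forward. Activity is the "proportion of patients who reaches an NfL increase at 14 days equal to or lower than the baseline level by five folds". The cutoff of five comes from an external cohort "showing a median increase of 12.8-fold at 14 days compared to baseline, with the first quartile equal to a fivefold increase". The arm with more responders wins. If the arms tie, the cutoff is raised by one unit at a time until they differ. Only the two MSC arms are compared, with 12 evaluable patients each. The article claims more than 80% probability of correct selection when responder proportions differ by 15 points.

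Step 2 uses a different quantity: "The endpoint will be the NfL at 14 days". Data analysis tests it on the log scale with a one-sided t test.

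Three other places bear on this. Neurofilament light as a pharmacodynamic marker describes a "progressive increase in plasma levels over the first 2 weeks after injury". Table 2 requires "Study drug (MSCs/placebo) administration start within 48 h from TBI". Secondary objectives lists blood sampling "daily for 3 days after TBI, at days 7 and 14 and at 1, 6 and 12 months". Randomisation is in permuted blocks stratified by centre. The article states no adjustment for baseline level or time since injury in the dose selection.

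**The concern.** The dose is ranked on one quantity and judged on another. The selection statistic is day-14 NfL divided by baseline NfL, reduced to yes or no at five. Two things are lost:

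- **Information.** A patient just under the cutoff counts the same as one far under it.
- **Precision.** Dividing by baseline carries all the baseline variation into the outcome, whether or not baseline predicts day 14. On a rising curve, part of that variation can come from differing times since injury.

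With 12 patients per arm neither loss averages out well. The choice commits all of Step 2 to one dose, so a wrong pick means that the better dose never reaches the primary test.

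**Working it through.** **Inputs from the article:** fold-rise median 12.8 and first quartile 5; 12 evaluable patients per dose arm; cutoff 5, raised by 1 on ties; Step 2 effect size 0.59 with 27 per arm, one-sided 10% error and 80% power.

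**Inputs assumed:** lognormal fold-rise; SD *s* of ln day-14 NfL between 0.7 and 1.8; correlation ρ between ln baseline and ln day-14 NfL from 0 to 0.7; a between-dose difference of 0.59 SD. The 0.59 is borrowed from the Step 2 comparison with placebo as an illustration. Reading it in SD units fits the article's sample size: 27 per arm gives 81% power.

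**1. The article's own figure.** Exact binomial selection at 25% against 40% responders, with ties split evenly, gives 78.2% at 12 per arm and 80.1% at 14. Simulating the actual tie rule gives 79.8% and 81.6%. At 10% against 25%, 12 per arm gives 83.2%. The claim of more than 80% is borderline at 12 per arm but broadly reproduced.

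**2. Spread of the fold-rise.** SD of ln fold = ln(12.8/5)/0.6745 = 0.940/0.6745 = 1.39.

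**3. Probability of picking the better dose.**

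- Unadjusted ln day-14 level: Φ(0.59 × √(12/2)) = Φ(1.445) = 92.6%, whatever *s* is.
- Mean ln fold, not dichotomised: Φ(0.59 × *s* × √6 / 1.394). At *s* = 1.0 this is Φ(1.037) = 85%.
- Stated rule and adjusted comparison: simulated with 40,000 trials per setting. The baseline SD *b* was set so that *s*² + *b*² − 2ρ*sb* = 1.394². The adjusted comparison fits one common slope on ln baseline.

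| SD of ln day-14 (assumed) | Stated rule | Mean ln fold | Unadjusted level | Adjusted for ln baseline |
|---|---|---|---|---|
| 0.7 | 72% | 77% | 93% | 92–98% (ρ 0 to 0.7) |
| 1.0 | 80% | 85% | 93% | 92–98% (ρ 0 to 0.7) |
| 1.39 | 88% | 93% | 93% | 93–98% (ρ 0.3 to 0.7) |
| 1.8 | 94% | 97% | 93% | 98% (ρ 0.7) |

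Some correlations are missing from the lower rows because no baseline SD is compatible with an SD of ln fold of 1.39. For a given *s*, the stated rule does not depend on ρ. The adjusted figure depends only on ρ: about 92% at 0, 93% at 0.3, 95% at 0.5 and 98% at 0.7.

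The *s* = 1.0 row is close to the article's own design case. A shift of 0.59 in ln fold moves responders from 25% to Φ((ln 5 − ln 12.8 + 0.59)/1.394) = 40%, the 15-point difference. There, the step from 80% to 85% is the cost of dichotomising, and the step from 85% to 93% is the cost of dividing by baseline.

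**4. How much of this is timing?** Assume that the 12.8-fold median refers to a 24 h baseline. For one untreated patient sampled at 6, 24 or 48 h, the chance of being a responder is then 22%, 25% or 30% if NfL rises log-linearly, and 7%, 25% or 42% if it rises linearly. With sampling times uniform over 6–48 h in both arms, timing explains 0.5% (log-linear) to 12% (linear) of the variance of ln fold. Standardising it would raise correct selection from 79.8% to 80.0% (log-linear) or from 79.9% to 81.1% (linear). On average, timing is a small part of the loss.

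**5. Chance imbalance.** With an assumed SD of ln baseline of 1, the difference in mean ln baseline between two arms of 12 has SD √(2/12) = 0.41, a factor of exp(0.41) ≈ 1.5. If baselines differ by 1.5-fold with no matching difference at day 14 and no dose effect, the rule picks the higher-baseline arm 72% of the time. If the inferior dose holds the higher baselines at 25% against 40%, correct selection falls to 60%. Baseline imbalance is already averaged into the table and should not be added to it.

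**The case against.** The strongest defence is that a pick-the-winner screen need not use the final endpoint, and that this one roughly meets its stated operating characteristic. Step 2 compares the chosen dose with randomised placebo on the day-14 level, so its endpoint does not use the baseline ratio. That stands: the point concerns how well Step 1 selects, not the validity of the Step 2 endpoint.

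Three stronger readings are tempting, and the article does not support them.

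- **That the rule favours the arm sampled later.** The 48 h limit is on starting study drug. The baseline draw time is not in the text shown and may be fixed in the timepoint figure or the full protocol. Both doses are also randomised concurrently, so timing is noise between arms. The 7%-to-42% range compares individual patients and cannot be set against a 15-point difference between arms.
- **That the rule rewards large initial injuries.** The article says that "initial serum NfL levels are predictive of clinical outcome", but if day-14 NfL is proportional to baseline, the ratio removes injury size. It over-corrects only if the log-log slope is below 1, and no slope is given.
- **That the plain day-14 level is always better.** It is not. At *s* = 1.8 and ρ = 0.7 the stated rule reaches 94% against 93%; at *s* = 2.0 and ρ = 0.8 it reaches 96% against 93%. The adjusted comparison gives 98% and 99% in those two cases, so the objection defeats the unadjusted alternative only.

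**Conclusion.** The point holds as one of efficiency and alignment. Step 1 ranks doses on a dichotomised ratio, and Step 2 tests a continuous day-14 level. In every feasible setting examined, the baseline-adjusted day-14 comparison selected the better dose more often than the stated rule. The gain ranged from about 26 points (72% to 98%, at *s* = 0.7 and ρ = 0.7) to about 3 points (96% to 99%, at *s* = 2.0 and ρ = 0.8). The size rests on the lognormal fold-rise, the illustrative 0.59 SD between doses, and an SD and a correlation that the article does not give. Nothing here shows bias between the doses or a flaw in the Step 2 test. It is a cheap improvement, worth making because the selection is irreversible within the trial.

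**What to change.** Among doses that pass the safety rule, select the one with the lower mean ln(NfL) at day 14, adjusted for ln baseline NfL and, where recorded, for hours from injury to the baseline sample. Report the five-fold responder proportion for each arm as descriptive only. The iterative tie rule is then no longer needed.

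The cost is wording and one small model on the 24 evaluable patients in the two MSC arms, using NfL samples already planned. There are two downsides. The simple responder count is no longer the basis for selection, and the stated Simon, Wittes and Ellenberg probability no longer applies. The probability of correct selection must be recalculated for the new rule, with the assumed SD and baseline-to-day-14 correlation stated.

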**Methods/design:**

The study will be conducted in two steps. Step 1 will enrol 42 patients, randomised in a 1:1:1 ratio to receive 80 million MSCs, 160 million MSCs or a placebo to establish safety and identify the most promising dose. Step 2 will enrol an additional 36 patients, randomised in a 1:1 ratio to receive the selected dose of MSCs or placebo. The activity of MSCs will be assessed by quantifying the plasmatic levels of neurofilament light (NfL) at 14 days as a biomarker of neuronal damage. It could be a significant breakthrough if the study demonstrates the safety and efficacy of MSC-based therapy for severe TBI patients. The results of this trial could inform the design of a phase III clinical trial aimed at establishing the efficacy of the first neurorestorative therapy for TBI.

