### Data analysis

The analysis of primary activity outcomes will be performed on the per-protocol (PP) population, including all randomised patients, without major eligibility violations criteria, who received the allocated treatment as specified in the protocol and with a follow-up of at least 14 days. Major violations in the eligibility criteria will be evaluated on a case-by-case basis in a pre-analysis meeting to define the population.

The safety analysis population will include all patients who have received the treatment. Each patient will be analysed in the arm received.

Frequency and percentages will describe the proportion of patients in each experimental group experiencing at least one SADR within 14 days from treatment administration.

In terms of NfL change from baseline to 14 days, the proportion of responder patients will be described through frequency and percentages. Regarding the NfL measured at 14 days, a one-sided Student's *t* test on the logarithmic scale will be performed to compare the experimental and control arms. Assumptions of Student's *t* test (i.e., normality of residuals and homoscedasticity) will be checked on a log scale using graphical (i.e., histograms and normal quantile plots) and formal methods (Shapiro–Wilk test for normality and Levene's test for equal variance). In case of failed assumptions, a proper data transformation will be considered. Univariable and multivariable generalised linear regression models will be used to evaluate the impact of the potential prognostic factors on the NfL at 14 days. Univariable and multivariable generalised linear mixed regression models for repeated measures will be used to evaluate the impact of treatment on longitudinal data.

Loss to follow-up patients and patients with missing values will contribute to the analysis of the secondary outcomes only for the time data are available. Univariable and multivariable generalised linear mixed regression models for repeated measures will be used to evaluate the impact of treatment on longitudinal MRI and blood biomarkers, and functional outcome.

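### When both doses pass safety, step 1 patients choose the dose and then enter the final test, so its one-sided error is about 11% to 13.5%, not 10%

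*Protocol article*

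**What the plan says.** Under Statistical design and sample size, Step 1, "12 evaluable patients will be analysed in each group". If both doses are judged safe, a responder is a patient whose NfL rises no more than fivefold from baseline to day 14, and "The experimental arm with a higher frequency of responders will be selected as the most promising in terms of activity". Ties are broken by raising the cutoff one unit at a time. Placebo patients play no part in the choice.

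Under Step 2 the endpoint is NfL at day 14. "The final analysis of biological activity will be performed by increasing the sample size to 27 evaluable patients in the experimental and control arms". The evaluable total of 66 is made up of 27 controls plus "12 in the experimental arm stopping at the first step and 27 in the experimental arm reaching the second step". The abstract agrees: "Step 2 will enrol an additional 36 patients, randomised in a 1:1 ratio".

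The target difference is given as follows: "The study is designed to detect an effect size of 0.59 on the logarithmic scale of the experimental to control arm". Both error rates for this comparison are then fixed by "setting a one-sided type I error rate of 10% and a power of 80" per cent. Under Data analysis, a one-sided Student's "test on the logarithmic scale will be performed to compare the experimental and control arms". No adjusted critical value, combination rule or adjusted estimate is mentioned.

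**The concern.** Day-14 NfL is the numerator of the fold change that picks the winning dose, and it is also the endpoint of the final test. The winner's 12 patients will tend to have low day-14 values partly by chance, and they supply 12 of the 27 values on the MSC side. The control side has not been filtered in this way. An unadjusted test then rejects too often when neither dose works, and the estimated effect is too favourable. This comparison is one of the two primary objectives and is meant to inform a phase III design. Its 10% one-sided level is already lenient, so the error rate should be what the plan says it is.

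**Working it through.** **1. Pooling.** Per-arm evaluable numbers go from 12 to 27, so 15 are new. Randomised: 14 + 36/2 = 14 + 18 = 32 per continuing arm, which matches 27/0.87 = 31.03 (the article gives 32) and 12/0.87 = 13.8 (14). The totals work only if the step 1 patients are in the final comparison.

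**2. The plan's own sample size.** Read 0.59 as a standardised difference. Power of the one-sided t test is 1 − F(t₀.₉₀; df = 2n − 2, ncp = 0.59·√(n/2)), with F the noncentral t distribution. For n = 26 it is 0.796. For n = 27 (ncp = 0.59·√13.5 = 2.17) it is 0.808. So 27 is the fixed two-arm size at the full 10%, with nothing set aside for selection.

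**3. Inputs to the error rate.**
- Fold change: median 12.8 and first quartile 5 (Step 1). If log-normal, the SD of ln fold is ln(12.8/5)/0.6745 = 0.940/0.6745 = 1.39.
- Correlation ρ between log fold change and log day-14 NfL: not given, so assumed over a range. If r is the baseline/day-14 correlation and k the ratio of baseline SD to day-14 SD (log scale), then ρ = (1 − rk)/√(1 + k² − 2rk). For example, r = 0, k = 0.5 gives 0.89; r = 0.5, k = 1 gives 0.50; r = 0.7, k = 1 gives 0.39; r = 0.9, k = 1 gives 0.22. It is positive whenever rk < 1.

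**4. Simulation under the global null.** Each simulated trial had 12 patients per MSC arm, the fivefold responder rule with its tie-break, 15 new patients in the chosen arm, 27 controls, and an unadjusted one-sided t test at 10%. There were 400,000 trials per row. A separate run of 600,000 agreed to within 0.1 percentage point and supplied the bias column.

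| ρ (assumed) | Type I error | Nominal level that would hold 10% | Bias towards MSC (SD) |
|---|---|---|---|
| 0 | 10.1% (10% within simulation error) | 0.099 | 0.00 |
| 0.25 | 10.9% | 0.091 | 0.01 |
| 0.5 | 11.8% | 0.084 | 0.03 |
| 0.7 | 12.4% | 0.079 | 0.04 |
| 0.85 | 13.0% | 0.076 | 0.05 |
| 1.0 (limit) | 13.5% | 0.073 | 0.06 |

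**5. Weighting for the safety gate.** Selection happens only if both doses pass. With a true SADR rate of 5% (the plan's acceptable rate), P(0 or 1 of 12) = 0.95¹² + 12·0.05·0.95¹¹ = 0.88. Both pass with probability 0.88164² = 0.777, and exactly one with 2·0.88164·0.11836 = 0.209. In the latter case the test runs at 10%. Overall error at ρ = 0.5 is 0.777·0.118 + 0.209·0.10 = 0.113. At ρ = 1.0 it is 0.777·0.135 + 0.209·0.10 = 0.126.

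**6. What an adjusted level costs.** In the formula of step 2 with n = 27, power is 78.1% at nominal 0.085, 76.0% at 0.075 and 74.8% at 0.07. Holding 80% would take 29 evaluable per arm at 0.085 and 32 at 0.07.

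**The case against.** The strongest reply is about size. This is a 78-patient academic phase II study with a deliberately loose alpha, testing a biomarker. A rise of one to three points on 10%, or a bias of 0.05 SD against a target of 0.59, is unlikely to change a phase III decision by itself. That stands, and it keeps the point at moderate.

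It also stands that the correlation is unknown. If baseline and day-14 NfL are strongly correlated, or baseline is the more variable of the two, ρ falls towards zero and the inflation almost disappears.

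A third reply is that the article is condensed, and the full protocol or an analysis plan may contain an adjustment. It may. But the article sizes the trial at the full unadjusted 10%, so any adjustment made elsewhere would take the stated power below 80% at 27 per arm.

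Three stronger readings are tempting and are not supported:
- **That the pooled test costs power.** If only one dose is active, overall power does fall below 80%, but mainly because some trials pick the inactive dose. When the active dose is the one picked, the unadjusted test rejects in about 81% to 83% of trials. The article's 80% concerns experimental against control at 0.59, and it treats correct selection separately.
- **That the error approaches 15%.** Choosing the dose on mean log day-14 NfL itself would give 14.7%, but the plan does not use that rule.
- **That one fixed nominal level, such as 0.075, is the answer.** Depending on ρ, it gives an actual error of about 7.4% to 10.2%.

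**Conclusion.** The point holds, at moderate severity. When both doses pass safety, the stated one-sided 10% is not held: it is about 11% to 13.5% for ρ from 0.25 to 1.0, and near 10% only if fold change and day-14 NfL are almost uncorrelated. Averaged over the safety gate, with each dose passing with probability 0.88, it is about 11.3% to 12.6% for ρ from 0.5 to 1.0. The effect estimate is biased towards benefit by up to about 0.05 SD (slightly more in the limiting case ρ = 1). These figures assume log-normal fold changes with the quoted median and quartile, both doses equal to placebo, and a correlation that the article does not give. The direction does not depend on the exact value, as long as the correlation is positive.

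**What to change.** Apply an adjusted final analysis only when a choice between two safe doses has been made, and keep 10% when one dose alone survives safety. Either of two tests would do:
- an inverse-normal combination of the step 1 and step 2 p-values, with weights √(12/27) and √(15/27) and a Dunnett intersection test in step 1 under closed testing;
- the same t test at a nominal level calibrated by simulation over a stated correlation range (about 0.073 to 0.091 for the ρ values of 0.25 to 1.0 above).

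Report a selection-adjusted estimate beside the ordinary one. Restate the 80% power as conditional on the selected dose having the 0.59 effect and at the adjusted level: about 75% to 78% in the fixed-design calculation at nominal 0.07 to 0.085 with 27 per arm. If none of this is adopted, at least replace the 10% by the simulated error rate and its assumptions.

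The cost is wording, a short simulation and a few points of power. No extra patients are needed unless the sponsor wants to keep 80% at the adjusted level, which would take 29 to 32 evaluable per arm. Testing only the 15 + 15 new patients would also remove the bias, but power would drop to about 62%, so it is not recommended.
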